# Acupuncture of different treatment frequency in knee osteoarthritis: a protocol for a pilot randomized clinical trial

**DOI:** 10.1186/s13063-019-3528-8

**Published:** 2019-07-11

**Keywords:** Knee osteoarthritis, Acupuncture, Treatment frequency, Clinical trial

## Abstract

**Background:**

This study aims to determine whether 3 sessions per week of acupuncture treatment is superior to 1 session per week of acupuncture treatment for symptomatic outcomes in knee osteoarthritis.

**Methods/design:**

This is a two parallel-group, assessor-blinded, randomized controlled trial. Sixty patients with knee osteoarthritis (Kellgren–Lawrence grade II or III) will be recruited and randomly allocated to receive 24 or 8 sessions (group M or group L) of acupuncture treatment in a 1:1 ratio. Patients in group M will receive 3 sessions per week of acupuncture for 8 weeks. Patients in group L will receive acupuncture once per week for 8 weeks. The primary outcome is the response rate—the percentage of patients achieving a decrease ≥ 2 points on a numerical rating pain scale and a decrease ≥ 6 points in the Western Ontario and McMaster Universities Osteoarthritis Index function score at 8 weeks compared with baseline. Secondary outcomes include pain, function, overall effect, quality of life, and treatment credibility and expectancy.

**Discussion:**

Three sessions per week of acupuncture treatment may be superior to 1 session per week of acupuncture treatment for symptomatic outcomes in knee osteoarthritis. Results of the study will be of great importance for the guidelines of clinical therapy.

**Trial registration:**

Clinicaltrials.gov, NCT03359603. Registered on 1 December 2017.

**Electronic supplementary material:**

The online version of this article (10.1186/s13063-019-3528-8) contains supplementary material, which is available to authorized users.

## Background

Knee osteoarthritis is a common and disabling condition, particularly in people over 50 years of age [1]. The estimated lifetime risk for knee osteoarthritis is approximately 40% in men and 47% in women [2]. In addition to the personal burden of knee osteoarthritis, there are substantial direct and indirect health-care costs particularly in terms of employment status, productivity and joint replacement surgery, making knee osteoarthritis a substantial public health problem [3].

There is currently no consensus on the best treatment to improve knee osteoarthritis symptoms. Pharmacologic modalities used to treat the symptoms of this disorder are associated with various side effects such as renal toxicity, serious gastrointestinal complications and cardiovascular events [4]. In fact, patients generally do not like taking medicines [5]. People with knee osteoarthritis prefer nonpharmacological options for pain relief and usually choose complementary medicine [6].

Nonpharmacological methods such as education and self-management, exercise and physical activity are recommended in the guidelines [7, 8]. However, the effect of exercise treatment decreases over time [9] and self-management education programs result in no or small benefits in people with knee osteoarthritis [10]. In addition, these methods as complex interventions can decrease adherence for individuals [11].

Acupuncture is one of the most common complementary and alternative medical therapies and a popular treatment for pain and dysfunction associated with musculoskeletal conditions, and the effects of acupuncture are maintained over time [12, 13]. In a systematic review of osteoarthritis guidelines, five of the eight guidelines that considered acupuncture recommended it as an osteoarthritis treatment modality [4]. However, the benefits of acupuncture remain highly controversial. In a meta-analysis of acupuncture for knee osteoarthritis including 10 randomized controlled trials with a total of 2007 patients from 1994 to 2014, the acupuncture group had significantly improved overall pain and physical function scores as compared with the sham acupuncture group [14]. In contrast, another meta-analysis and several large trials indicated that real acupuncture had no significant effect on osteoarthritis pain and function as compared to sham acupuncture [15–17].

Based upon previous high-quality studies, we speculate that the clinical effectiveness of acupuncture for knee osteoarthritis may relate to treatment frequency. The treatment frequency in acupuncture trials with knee osteoarthritis which showed negative results [17, 18] is significantly lower than that in other trials showing positive results [19, 20]. Furthermore, acupuncture is superior to sham acupuncture on symptomatic outcomes in patients with chronic pain who received 3 or more sessions of treatment per week [21–25]. Meanwhile, 1 session or no acupuncture session per week usually showed no significant improvement in pain with acupuncture compared with sham acupuncture [17, 18]. However, there are no currently universally accepted treatment frequency criteria. The frequency of acupuncture treatment in patients with knee osteoarthritis is no more than twice per week in most trials, while it is usually 3–5 sessions per week in clinical practice in China. Studies also suggested that acupuncture treatments once a day or every other day maybe reasonable in chronic painful conditions [26]. Accordingly, we designed the current trial to compare the effects of different acupuncture sessions (3 sessions per week versus 1 session per week) in a pilot randomized controlled trial of knee osteoarthritis. The hypothesis is that 3 sessions per week compared with 1 session per week of acupuncture treatment will lead to better symptomatic outcomes.

## Methods

### Study design

This is a pragmatic, parallel, two-armed randomized controlled exploratory study with 8-week follow-up. The protocol has been registered on ClinicalTrials.gov (No NCT03359603) and will be conducted in accordance with the Declaration of Helsinki. The study will be reported in accordance with the Consolidated Standards of Reporting Trials (CONSORT) statement and its relevant extensions to randomized pilot and feasibility trials [27]. The protocol was reported in accordance with the Standard Protocol Items (SPIRIT) (Additional file 1) .The study patient flow outline is shown in Figs. 1 and 2.

**Fig. 1 Fig1:**
[figure not shown]
Trial flow chart: Consolidated Standards of Reporting Trials CONSORT diagram. OA osteoarthritis

**Fig. 2 Fig2:**
[figure not shown]
Template of content for the schedule of enrolment, interventions and assessments. AFT after first treatment; NRS numerical rating scale; SF-12 Medical Outcomes Study 12-item Short-Form Health Survey; WOMAC Western Ontario and McMasters Universities Osteoarthritis Index

### Study setting, recruitment and ethics

The recruitment will be conducted at Beijing Hospital of Traditional Chinese Medicine Affiliated to Capital Medical University. The study plans to recruit 60 patients with knee osteoarthritis using acupuncture students to do the recruiting. The study was approved by the medical ethical review committee of Beijing Hospital of Traditional Chinese Medicine Affiliated to Capital Medical University (No. 2017BL-076-01). Patients will be recruited through WeChat (a social networking site), outpatient units and print advertisements. People willing to participate in the study will be invited to contact the clinical research coordinator (CRC) by telephone. The CRC will perform a preliminary screening of people for inclusion and exclusion criteria, and then, if appropriate, schedule a face-to-face baseline visit with a senior specialist in physical and rehabilitation medicine. Patients will also be referred for radiographic evaluation. All eligible patients will provide written informed consent (Additional file 2). The CRC will discuss the study in detail (i.e., the study purpose, procedures and time commitment, as well as the potential risks and benefits associated with participation in the study) with potential patients and obtain written informed consent. The confidentiality of patient records will be protected. At the time of enrolment, each patient will be assigned a unique randomization number, which is the only direct identifier included on all case report forms.

### Inclusion criteria

Age 45–75 years, male or female.Diagnosis of knee osteoarthritis according to the American College of Rheumatology (ACR) criteria [28].Symptoms have been present for more than 6 months.Radiologic confirmation of knee osteoarthritis (Kellgren–Lawrence grade [29] II or III in the recent 6 months).An average knee pain severity over the past week of ≥ 4 out of 10 on an 11-point numerical rating scale (NRS) [30].Agreed to refrain from the use of any analgesics during the trial (paracetamol sustained-release tablets will be given to patients if their pain intensity reaches ≥ 8 out of 10 on an 11-point NRS).Signed informed consent.

### Exclusion criteria

History of knee surgery or waiting for surgery (knee replacement or knee arthroscopy).Knee pain caused by other diseases (such as joint loose bodies, severe effusion of the joint cavity, infection, malignant tumors, autoimmune diseases and trauma).History of arthroscopy within 1 year or intra-articular injection within 4 months.History of receiving acupuncture treatment within 3 months.Severe acute/chronic organic or mental diseases.Pregnant and lactating women.Coagulation disorders (such as hemophilia, etc.).Participation in another clinical study in the past 3 months.History of a cardiac pacemaker, metal allergy or needle phobia.

### Randomization and blinding

Patients will be randomly assigned (on a 1:1 ratio) to the more frequent acupuncture treatment group (group M) or the less frequent acupuncture treatment group (group L). The randomization sequence will be computer generated by independent research staff with SAS 9.3 software, using block randomization with a block size of six via a central randomization system. The randomization sequence will be embedded into the software (Beijing Guide Technology Co, Ltd). The CRC will input the patient information on a tablet computer and will be given a random number. The randomization protocol will be designed by a statistician ([name]) of Fuwai Hospital, China Academy of Medical Science who is not involved in the later statistical work of the study.

The outcome assessor and data analyst will be blinded to group assignments. The acupuncturist and patients will not be blinded because of the nature of the intervention. Patients’ allocated interventions will not be revealed until the statistical analysis is completed.

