### Sample size

The current study is designed as a pilot study to explore symptomatic improvement in patients with knee osteoarthritis receiving 3 sessions per week of acupuncture compared to 1 session per week. Acupuncture as a complex intervention is different from drugs. If the acupoints in the study were changed, then the effectiveness of the acupuncture would be altered. Consequently, we do not use data from the literature to calculate the sample size. We based our sample size on the response rate. Based on our previous study (unpublished) and clinical experience, the sample size is calculated to provide 80% power if 70% of group M achieved a decrease ≥ 2 points on the NRS and a decrease ≥ 6 points in WOMAC function score at 8 weeks, compared with 30% of group L, at a two-tailed α level of 0.05. This requires a total of 60 participants, allowing for 20% dropout.

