## Discussion

This study is designed to explore an effective acupuncture method for knee osteoarthritis.

We chose a frequency of 3 sessions per week as one kind of electro-acupuncture intervention, because 3 sessions per week is most commonly used in clinical practice in China to treat chronic pain. We chose a frequency of once per week as another intervention, because electro-acupuncture treatment once per week was usually used in previous studies. The study is a single-site randomized clinical trial. A single-site trial might be helpful in the aspect that the quality of the study procedure will be better controlled in a single site than in multiple sites. One potential limitation of this study is that the unblinded treatment might theoretically influence reporting or measurement of the outcomes, thus introducing bias. Therefore, we will use an Expectation and Credibility of treatment rating scale to measure the patients’ attitudes to acupuncture.

The information obtained from the exploratory study will inform the decision to conduct a full-scale randomized controlled trial to test the frequency dependence of acupuncture, which will add to the current small body of high-quality evidence that is available on the optimal number of sessions of acupuncture for the management of knee osteoarthritis.

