## Trial status

This trial is currently recruiting patients.

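### A single block size of six, published during recruitment at one open-label site, lets enrolling staff who know earlier allocations deduce up to a quarter of the rest

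*Protocol article*

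**What the plan says.** Under Randomization and blinding, the protocol article has a computer-generated 1:1 sequence, "using block randomization with a block size of six via a central randomization system". Independent staff generate it, and a statistician from another hospital designs the scheme. No varying sizes or strata are mentioned, and nothing says that the block size is kept from site staff.

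On who knows the arm, the same section says "The acupuncturist and patients will not be blinded because of the nature of the intervention" and "The outcome assessor and data analyst will be blinded to group assignments". The clinical research coordinator (CRC) is not on the blinded list. Group M attends three times a week and group L once (sections Group M and Group L).

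On who controls entry, Study setting, recruitment and ethics says "The CRC will perform a preliminary screening of people for inclusion and exclusion criteria". The CRC also takes consent and, under Randomization and blinding, enters the patient on a tablet and receives a random number. Between screening and entry come a baseline visit with a senior specialist and a radiograph.

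The Discussion says "The study is a single-site randomized clinical trial". Trial status says "This trial is currently recruiting patients". The article is dated 11 July 2019.

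**The concern.** In a block of six at 1:1, each arm has three places. Once one arm is full, every later allocation in that block is known. One site means that one sequence is filled in order, and the visit pattern shows each patient's arm soon after entry. A person who knows the block size can therefore keep a running count. Publication made that size available to everyone while patients were still being entered.

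Foreknowledge matters because it permits selection: delaying, encouraging or discouraging a particular patient according to the arm that comes next. The Background states a hypothesis in favour of group M. The primary outcome is a patient-reported responder rule compared by an unadjusted χ² test, so an imbalance in who enters each arm would pass straight into the result. Blinded assessment and blinded analysis act after entry and cannot undo it.

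**Working it through.** **Inputs.** Block size 6 and ratio 1:1 (Randomization and blinding). Total 60, from 70% against 30% response, 80% power, two-sided α 0.05 and 20% dropout (Sample size).

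**The plan's own figure.** The article gives no figure for predictability, but its total can be reproduced. With pooled variance under the null and no continuity correction:

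n per arm = [1.96 × √(2 × 0.5 × 0.5) + 0.8416 × √(0.7 × 0.3 + 0.3 × 0.7)]² / 0.4² = (1.386 + 0.545)² / 0.16 ≈ 23.3, so 24.

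24 / 0.8 = 30 per arm, 60 in total. This agrees with "This requires a total of 60 participants, allowing for 20% dropout". It makes 60 / 6 = 10 complete blocks.

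**Certain allocations in a block of six.** There are C(6,3) = 20 equally likely orders. An allocation is certain when one arm already has its three patients.

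| Position | When certain | Probability |
|---|---|---|
| 1 to 3 | never | 0 |
| 4 | first three all in one arm: 2 of 20 | 0.10 |
| 5 | last two in the same arm: 2 × C(4,1) = 8 of 20 | 0.40 |
| 6 | always | 1.00 |

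The sum is 1.5 per block. The closed form 2m/(m + 1) with m = 3 gives the same. So 1.5 / 6 = 25%, and 10 × 1.5 = 15 of 60: the last patient of each block (10) plus an expected 5 more.

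**Exposure from publication alone.** If r patients in complete blocks remained to be randomised in July 2019, the expected number certain is 0.25 × r. The article does not give r. For illustration, r = 12 gives 3, r = 30 gives 7.5 and r = 60 gives 15.

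**Best guess.** Guessing the arm with more places left, and tossing a coin when they are equal, is right for 4.1 of 6 on average. That is 68.3%, against 50% under simple randomisation.

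**After the change.** Simulated trials of 60, with an observer who knows the set of sizes and all earlier allocations but not the order of the sizes:

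| Scheme | Certain | Best guess correct |
|---|---|---|
| Fixed 6 | 25% | 68.3% |
| Fixed 8 (exact) | 20% | 66.6% |
| Random 4 or 6 | about 5% | about 69% |
| Random 4, 6 or 8 | about 2% | about 68% |

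With 4, 6 or 8, about 27% of simulated trials ended unbalanced at 60, nearly all at 31 against 29.

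**The case against.** The strongest reply is that the list is well protected. It is generated by independent staff, designed outside the hospital and delivered by central software, and the article does not say that anyone at the site knew the block size before publication. This stands, and it makes 25% a ceiling. A reader might infer that 15 of the 60 allocations were in fact predictable. The documents do not support that: it needs one person who knew the size and the full ordered history from the first patient onward. Publication exposes only patients not yet randomised, and their number is not given.

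The CRC receives a number, and the article does not say that it shows the arm. It also says that allocations stay undisclosed until the analysis is finished. That cannot hold for unblinded patients and acupuncturists, though it may be meant for other roles. Following the visit pattern in entry order is plausible, not documented, and the arm shows only once visits begin.

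A reader might also infer that the CRC alone decides who enters. The CRC's screening is preliminary, and a specialist visit and radiograph follow. What remains open is the timing of entry and the consent discussion.

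Finally, fixed blocks deliver exactly 30 per arm, and the trial is a pilot. Both are true. Yet the trial makes a powered two-sided comparison of response rates, and an end difference of two patients is a small price.

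**Conclusion.** The point holds as a vulnerability in allocation concealment, not as evidence that selection occurred. Its size is up to 25% of allocations known with certainty (1.5 of 6 per block), at most an expected 15 of 60. It rests on three assumptions: the observer knows that the block size is six, knows all earlier allocations in order, and has some influence on entry. With partial knowledge, or with knowledge only since publication, the number is lower. The effect on the difference in response rates cannot be sized from the article.

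A reader might take the 68% best-guess rate as a second harm that varying blocks would cure. They would not: it stays near 68%. What falls is certainty, from 25% to about 2%, and certainty is what makes deliberate steering reliable. This is a worthwhile, cheap improvement, and no ground to question the trial as a whole.

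**What to change.** For the allocations that remain, have the independent statistician regenerate the sequence with randomly varying block sizes and load it into the central system. The amendment should say that sizes vary at random and leave out the set, which should be withheld from site staff and public documents until recruitment closes. The sizes 4, 6 and 8 are used here only to show the gain. The 2% assumes that the set is known, so withholding it is an added safeguard.

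The new sequence is best started after the open block of six is full, without announcing the point of change. Abandoning a block part-way could leave a difference of up to three patients.

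The cost is a new list, a short amendment and an end imbalance, mostly 31 against 29, in roughly a quarter of realisations. The report should give both schemes and state who knew the block size and from when. It should not claim that predictability was removed.

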### Interventions

The treatment strategies for acupuncture are generally considered a pragmatic compromise between the need for some standardization and the need for individualization. This treatment is based on a distinguished Chinese textbook, as well as traditional Chinese medicine meridian theory to treat *Bi* syndrome. Furthermore, the therapy was discussed with experts in the field of acupuncture.

The most important local points in the literature were chosen as obligatory points. Therefore, the following five local points have to be used for every treatment session on the affected knee: ST 35, EX-LE5 (Neixiyan), LR 8, GB 33 and an Ahshi point. Another three customized acupoints should be chosen for therapy in accordance with the individual localization of the meridians that traverse the area of the most painful point, with the intent of optimizing efficacy. ST34, ST36, ST32, ST40 and EX-LE2 will be used for pain at the stomach meridian. GB31, GB36, GB34, GB39 and GB41 will be used for pain at the gallbladder meridian. BL39, BL40, BL57 and BL60 will be used for pain at the bladder meridian. LR7, SP9, SP10, KI10, SP4, SP6, LR3 and KI3 will be used for pain at the three-yin meridians of the foot (Table 1). The selection of the three customized acupoints will be based on the experience of the acupuncturist. Therefore, the number of needles used is eight (unilateral).

**Table 1 Tab1:** Locations for acupuncture

Acupoint	Location
ST 35 (Du bi)	On the anterior aspect of the knee, in the depression lateral to the patellar ligament
EX-LE5 (Nei xi yan)	On the anterior aspect of the knee, in the depression medial to the patellar ligament
LR8 (Ququan)	On the medial aspect of the knee, in the depression medial to the tendons of the semitendinosus and the semimembranosus muscles, at the medial end of the popliteal crease
GB33 (Xi yang guan)	On the lateral aspect of the knee, in the depression between the biceps femoris tendon and the iliotibial band, posterior and proximal to the lateral epicondyle of the femur
Ashi point	The point where the patient feels most pain
ST32 (Fu tu)	On the anterolateral aspect of the thigh, on the line connecting the lateral end of the base of the patella with the anterior superior iliac spine, 6 cun^a^ superior to the base of the patella
ST 34 (Liang qiu)	On the anterolateral aspect of the thigh, between the vastuslateralis muscle and the lateral border of the rectus femoris tendon, 2 cun superior to the base of the patella
ST 36 (Zu san li)	3 cun directly below ST35, and one finger-breadth lateral to the anterior border of the tibia
ST40 (Feng long)	On the anterolateral aspect of the leg, lateral border of the tibialis anterior muscle, 8 cun superior to the prominence of the lateral malleolus
EX-LE2 (He ding)	On the anterior aspect of the thigh, in the depression superior to the base of the patella
GB31 (Fengshi)	On the lateral aspect of the thigh, in the depression posterior to the iliotibial band where the tip of the middle finger rests, when standing up with the arms hanging alongside the thigh
GB 34 (Yang ling quan)	On the fibular aspect of the leg, in the depression anterior and distal to the head of the fibula
GB 36 (Waiqiu)	On the fbular aspect of the leg, anterior to the fibula, 7 cun proximal to the prominence of the lateral malleolus
GB39 (Xuanzhong)	On the fbular aspect of the leg, anterior to the fibula, 3 cun proximal to the prominence of the lateral malleolus
GB41 (Zulin qi)	On the dorsum of the foot, distal to the junction of the bases of the fourth and fifth metatarsal bones, in the depression lateral to the fifth extensor digitorum longus tendon
BL39 (Wei yang)	On the posterolateral aspect of the knee, just medial to the biceps femoris tendon in the popliteal crease
BL40 (Wei zhong)	On the posterior aspect of the knee, at the midpoint of the popliteal crease
BL57 (Cheng shan)	On the posterior aspect of the leg, at the connecting point of the calcaneal tendon with the two muscle bellies of the gastrocnemius muscle
BL60 (Kun lun)	On the posterolateral aspect of the ankle, in the depression between the prominence of the lateral malleolus and the calcaneal tendon
LR 3 (Tai chong)	In the depression anterior to the junction of first and second metatarsal bones
LR 7 (Xi guan)	On the tibial aspect of the leg, inferior to the medial condyle of the tibia, 1 cun posterior to SP9
KI 3 (Tai xi)	On the posteromedial aspect of the ankle, in the depression between the prominence of the medial malleolus and the calcaneal tendon
KI10 (Yin gu)	On the posteromedial aspect of the knee, just lateral to the semitendinosus tendon, in the popliteal crease
SP4 (Gong sun)	On the medial aspect of the foot, anteroinferior to the base of the first metatarsal bone, at the border between the red and white flesh
SP6 (San yin jiao)	On the tibial aspect of the leg, posterior to the medial border of the tibia, 3 cun superior to the prominence of the medial malleolus
SP 9 (Yin ling quan)	On the tibial aspect of the leg, in the depression between the inferior border of the medial condyle of the tibia and the medial border of the tibia
SP 10 (Xuehai)	On the anteromedial aspect of the thigh, on the bulge of the vastus medialis muscle, 2 cun superior to the medial end of the base of the patella

^a^1 cun (≈ 20 mm) is defined as the width of the interphalangeal joint of the patient’s thumb

Treatment will be performed with sterilized disposable steel needles, 0.30 mm × 25 mm or 0.30 mm × 40 mm (Huatuo disposable acupuncture needle; Suzhou, Jiangsu, China). The depth of needling should be 10–30 mm, depending on the point location. Needles will be stimulated manually for 10 s to achieve “De Qi”. Paired alligator clips will be attached transversely to the needle holders at LR 8-GB 33 and two other customized acupoints. An electric stimulator (HANS-200A acupoint nerve stimulator; Jisheng, Nanjing, China) will be applied to the four acupoints. The electro-acupuncture stimulation will last for 30 min with a dilatational wave of 2/100 Hz and a current intensity (0.1–1.0 mA) depending on the patient’s comfort level (preferably with skin around the acupoints shivering mildly without pain). Other needles will be manipulated for 10 s during the treatments. If both knees are affected, both knees will be treated with acupuncture as indicated. However, the electric stimulator will be used on only one knee (more painful).

The acupuncturist will be required to have a Chinese medicine practitioner license and have been qualified for at least 10 years. Paracetamol sustained-release tablets (Tylenol; Shanghai Johnson Pharmaceutical Co., Ltd.) will be given to patients if their pain intensity is ≥ 8 out of 10 on an 11-point NRS. Acupuncture treatment will be discontinued if the patients suffer from any adverse events and the acupuncture physicians can decide to terminate the trial.

